## 2.9 Conceptual Framework

Figure 1 shows the framework for improving maternal health behaviour using trained religious leaders in maternal health promotion. This conccptual framework is adapted by reviewing different literatures. Trained religious leaders are expected to improve understanding of pregnant mothers on key maternal health behaviour including ANC, SDS, BPCR and knowledge of obstetric danger signs. The religious leaders’ maternal health behaviours messaging, in addition to the existing services, it is expected to increase pregnant mothers access to maternal health information. This will influence maternal health behaviours that will result in improved maternal health service utilizations and knowlwdge and recognition obstetric dangers signs.

Figure 1: Trained religious leaders led maternal health communication and behavioural change process frame work to improve maternal health service utilization.

**Change: psychosocial**

- Knowledge
- Attitude
- Perception of Pregnancy Risk
- Self-efficacy

**Change: practice**

- ANC utilization
- Skilled delivery service utilization
- BPCR

**Trained religious leaders led maternal health education.**

- Group education approach
- IEC materials; flip chart, card and poster
- Case study
- Monitoring and follow up
- Credibility and popularity of trained religious leaders
- Completeness and accuracy of message

**Socio-demographic and economic characteristics**

- Age
- Ethenicity
- Religion
- Income
- Marital status
- Educational status
- Occupation
- Family size
- Average distance from nearest HC

**Reproductive history of pregnant mothers**

- Parity
- Age at pregnancy
- Still birth
- Abortion
- Home delivery
- Institutional delivery
- Neonatal death

## 2.10 Significance of the study

The government of Ethiopia has taken maternal and neonatal health and underlying accessibility and quality of healthcare into account, with the global targets of the Sustainable Development Goals (SDGs) to reduce the maternal mortality ratio to less than 70 per 100,000 live births and to reduce the neonatal mortality rate to as low as 12 per 1,000 live births by 2030. But the proportion of pregnant women who have care during delivery is universally lower than those who receive ANC. Poor, rural women in sub-Saharan Africa and South Asia are the least likely to receive antenatal, delivery or PNC. Different studies on factors influencing the utilization of maternity health services were done in the country and abroad. In Ethiopia, underutilization of the existing maternal health service is a major problem. This study is designed to use religious leaders to empower the community with knowledge and skill for better utilization of existing service for improvement of maternal and new-born health. It is anticipated that the study will provide impetus for the mainstreaming of involvement of religious leaders in maternal and new-born health. It is hoped that future programmes will re-design the current involvement of religious leaders in maternal and new-born health.

# Objectives

## 3.1 General objective

The overall goal of this study is to develop understanding of contributions of religious leaders to maternal health promotion and evaluate effectiveness of trained religious leaders’ engagement in maternal health education versus usual care on maternal health service utilizations. The details of study design, sample size, sampling technique and sampling procedure for each specific objective are discussed in method section.

## 3.2 Specific objectives

**Objective 1**: To assess effectiveness of trained religious leaders’ engagement in maternal health education in improving knowledge and recognitions of danger signs during pregnancy and child birth.

**Objective 2**: To assess effectiveness of trained religious leaders’ engagement in maternal health education on antenatal care service utilization

**Objective 3**: To assess effectiveness of trained religious leaders’ engagement in maternal health education on skilled delivery service utilization

**Objective 4**: To develop and validate religious’ leaders maternal health education engagement scale: elicitation study on mothers’ perception on religious leaders based maternal health promotion then scale development

**Objective 5**: To explore perception of religious leaders in promoting maternal and child health in rural setting.

# Hypothesis

We hypothesize that trained religious leaders’ engagement in maternal health education will increase the proportion of antenatal care, skilled delivery service utilizations and knowledge of danger signs during pregnancy, labor and child birth and neonatal danger signs.

# Chapter four Methods and Materials

## 4.1 Study settings and period

This study will be conducted in the two rural districts (Lemo and Amaka) of Hadiya Zone in Southern Ethiopia. Hadiya zone is divided into 13 rural Districts and two administrative towns with total of 329 kebeles from which 303 of them rural and 26 of them were urban. Each district is divided into kebeles**;** the lowest administrative units in Ethiopia. Hadiya Zone hosts a total of 1,573,841 populations with a total area of 3542.66 Km^2^. Hadiya zone has an estimated 54455 pregnant mothers. Population of the Lemo District is 148,339. From this 73,390 are males and 74,950 are females. There are 34,563 women in reproductive age group from which 5133 is expected pregnancy. Total population of Amaka district is 80857, 4125 are females and 39622 is males. Expected pregnancy is 2797. Protestant, orthodox and Muslim are the three dominant religions in Hadiya zone. 75.35% of the population are [Protestants](https://en.wikipedia.org/wiki/P%27ent%27ay), 11.13% are [Muslim](https://en.wikipedia.org/wiki/Islam_in_Ethiopia), 8.45% are Ethiopian Orthodox Christians, and 4.31% are [Catholic](https://en.wikipedia.org/wiki/Roman_Catholicism_in_Ethiopia). This study will be conducted between October, 2022 annd May, 2023.

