## 4.14 Cluster and individual selection

Health posts are eligible for trial. All 40 health post units in the selected districts are eligible and 12 health posts are randomly selected for the trial using a computer random number generator. Pregnant mothers less than or equal to 20 gestational age are eligible to participate in the trial if they are living in the villages within the selected health post village areas. Baseline surveys will be commenced in May 2022 and end line surveys are scheduled to begin after four months of intervention.

The pregnancy surveillance for this study will be conducted among currently married women of reproductive age (15–49 years) permanently living in the selected districts. A pregnancy test will be done for the study women at the beginning of the surveillance. Identifying pregnant women will be a two-step process. First, all women will be screened using pregnancy screening questions adapted from the Kenya family planning enrolment questionnaire as published in the Lancet (Stanback J et al, 199) (Table 2). If the answer to at least one of the six pregnancy screening questions is ‘yes’, pregnancy will be ruled out. Women who respond in a way that suggested the possibility of being pregnant is asked to provide a urine sample for a pregnancy test, which will be done using a dipstick in the respondent’s home. Once pregnancy is detected, the women will be recruited for the trial study.

Table 2 Pregnancy screening questions adapted from Kenya family planning screening questions

| S/No | Items | Yes or No |
| --- | --- | --- |
| 1 | Have you given birth in the past 4 weeks? |  |
| 2 | Are you less than 6 months post-partum or fully breastfeeding and free from menstrual bleeding since you had your child? |  |
| 3 | Did your last menstrual period start with in the past 7 days? |  |
| 4 | 4 Have you had a miscarriage or an abortion in the past 7 days? |  |
| 5 | Have you abstained from sexual intercourse since your last menses? |  |
| 6 | Have you been using a reliable contraceptive (pills, injectable, and Norplant) method consistently and correctly? |  |

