**Participant timeline**

Clusters will be enrolled and randomized to trial arms in June 1, 2022. Baseline recruitment and interviewing of women within study clusters began in June 5, 2022 and will be completed after four months of intervention.

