**End line Data collection**

The same procedure with the baseline data will be repeated to collect the end line data after one month of delivery. Six data collectors with health background will be used to collect the data. Two supervisors will be assigned to check for the daily activity, consistency, and completeness of the questionnaire and to give appropriate support during the data collection process. The data collectors and the supervisors will be assigned to a different cluster of a given district.

Qualitative Data collection

Focus group discussions and in-depth interviews among religious leaders and pregnant mothers will be conducted. Trained graduate research assistants will conduct Focus group discussions and in-depth interviews. Data will be collected by recording interviews by audiotape. Brief field notes will be taken during interviews. Field notes will be carefully taken during data collection and analysis. These notes will collect observations and assumptions about what will be heard or observed and personal narratives about what will be felt by the researcher during an interview.

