## 4.21 Ethical consideration

All procedures involving the research will be approved by Jimma University institute of Health ethical review board. Permission to undertake the study will be obtained from the regional, Zonal and district administration and health offices of the study area. After the identification of eligible pregnant mothers, the nature and purpose of the study will be explained along with their right to refuse. Written and informed consent will be obtained from all study participants. The right of the participant to withdraw from the study at any time will be respected. The data will not be accessed by a third person, except investigators, and will be kept confidential. The study will be registered at clinicaltrials.gov.

| S. No | Activities | 15/03/21 -20/03/21 | 01/04/21 – 20/08/2021 | 02/09/21 – 02/10/21 | 09/11/201 | 23-30/12/21 | 1-20/01/22 | 20/02/23 – 23/03/23 | 20/05/23 – 25/09/23 | 22/10/23- 23/11/23 | 30/12/23 – 1/03/203 | Responsible body | Remark |
| --- | --- | --- | --- | --- | --- | --- | --- | --- | --- | --- | --- | --- | --- |
|  | Discussing on title and fixing with my promoters |  |  |  |  |  |  |  |  |  |  | [name] & Promoters |  |
|  | Preparation of dissertation proposal |  |  |  |  |  |  |  |  |  |  | [name] |  |
|  | Preparation of data collection tools |  |  |  |  |  |  |  |  |  |  | [name] |  |
|  | Sending proposal to promoters |  |  |  |  |  |  |  |  |  |  | [name] |  |
|  | Accepting promoters’ comments and suggestions, modifying proposal accordingly |  |  |  |  |  |  |  |  |  |  | [name] & Promoters |  |
|  | Submission of proposal to department and Doctoral School |  |  |  |  |  |  |  |  |  |  | [name] & Promoters |  |
|  | Proposal defence |  |  |  |  |  |  |  |  |  |  | [name] |  |
|  | Receiving ethical clearance |  |  |  |  |  |  |  |  |  |  | [name] |  |
|  | Base line data collection |  |  |  |  |  |  |  |  |  |  | [name], data collectors and supervisors |  |
| 11 | Intervention for study subjects |  |  |  |  |  |  |  |  |  |  | [name] and trained religious leaders |  |
| 12. | End line data collection |  |  |  |  |  |  |  |  |  |  | [name], data collectors and supervisors |  |
| 13 | Analysis of data |  |  |  |  |  |  |  |  |  |  | [name] & Promoters |  |
| 14 | Manuscript preparation |  |  |  |  |  |  |  |  |  |  | [name] & Promoters gust & student |  |
| 16 | Manuscript submission to Journals |  |  |  |  |  |  |  |  |  |  | [name] & Promoters |  |

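### The protocol's calendars cannot all be true, and the October 2022 to May 2023 window does not hold an end line one month after delivery for women who enter early in pregnancy

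*Protocol*

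**What the plan says.** Section 4.1 fixes the study period: "This study will be conducted between October, 2022 annd May, 2023".

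Section 4.14 gives another start: "Baseline surveys will be commenced in May 2022 and end line surveys are scheduled to begin after four months of intervention".

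The Participant timeline gives a third: "Clusters will be enrolled and randomized to trial arms in June 1, 2022", followed by "Baseline recruitment and interviewing of women within study clusters began in June 5, 2022 and will be completed after four months of intervention".

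The work plan (Table 5, after section 4.21) has date columns that run beyond May 2023, among them 20/05/23 to 25/09/23 and 22/10/23 to 23/11/23. The marks linking activities to columns are not legible in the copy at hand. The Summary puts the whole project at about one year.

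On the order of events, section 4.17 places the pre-intervention survey after randomisation and allocation, and gives baseline data collection 15 days.

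On the end line, section 4.17 says: "The same procedure with the baseline data will be repeated to collect the end line data after one month of delivery". Sections 4.11, 4.13 (intervention table), 4.14 and the opening of 4.17 tie it to four months instead.

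Section 4.5 admits women below 20 weeks of gestation and sets no lower limit. Section 4.8 bases the sample size on skilled delivery and allows 10% loss to follow-up. On registration, section 4.21 says: "The study will be registered at clinicaltrials.gov". Ethics approval is also in the future tense there.

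**The concern.** The calendar decides two things that matter for the analysis.

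The first is the order of baseline and allocation. A baseline in May 2022 precedes randomisation on 1 June; a baseline from 5 June follows it. In a cluster trial, whether women are recruited before or after the clusters' allocation is known bears on selection bias, so the protocol should not leave it open.

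The second is whether the end line can take place. Skilled delivery can be recorded only once the birth has happened, and the post-delivery rule in 4.17 adds a month. A window of eight months at most, combined with entry at any gestation below 20 weeks, may close before the earliest entrants reach that interview. Missing interviews would then be concentrated among women with low gestation at entry and would not be spread at random.

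**Working it through.** **Dates side by side**

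| Place | Start | Order and length |
|---|---|---|
| 4.1 | October 2022, ending May 2023 | not stated |
| 4.14 | baseline May 2022 | before the 1 June randomisation |
| Participant timeline | randomisation 1 June, recruitment 5 June 2022 | baseline after randomisation; literally, complete only after four months of intervention |
| 4.17 | no date | baseline after randomisation; 15 days |
| Work plan | columns into late 2023 | clearance listed before baseline |

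No single calendar satisfies all rows. This part needs no assumption.

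**Does the 4.1 window hold the post-delivery interview?**

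Inputs from the protocol: the widest reading of 4.1, 1 October 2022 to 31 May 2023, is 242 days (34.6 weeks); baseline takes 15 days; entry is below 20 weeks; the end line is one month after delivery. Assumptions not in the protocol: birth at 40 weeks, one month = 30 days, and gestation at entry uniform between a lower limit L and 20 weeks.

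For a woman interviewed b days after 1 October, the minimum gestation at entry is 40 - (242 - 30 - b)/7.

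- b = 0: 40 - 212/7 = 9.7 weeks.
- b = 15 (16 October): 40 - 197/7 = 11.9 weeks.

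Share missed = (minimum - L)/(20 - L). For L = 5 this is (9.7 - 5)/15 = 31% and (11.9 - 5)/15 = 46%. For other limits:

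| L (weeks) | b = 0 | b = 15 | mean over 15 days | mean, birth at 39 weeks |
|---|---|---|---|---|
| 0 | 49% | 59% | 54% | 49% |
| 4 | 36% | 49% | 42% | 36% |
| 5 | 31% | 46% | 39% | 32% |
| 6 | 27% | 42% | 34% | 27% |
| 8 | 14% | 32% | 23% | 15% |

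The means put b = 7.5, so the minimum is 40 - 204.5/7 = 10.8 weeks (9.8 for birth at 39 weeks). They span roughly 15-55%. If all women enter at 13 weeks or later, both thresholds are passed and the share is 0%.

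**Women not yet delivered on 31 May**

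Drop the 30 days: the minimum is 40 - 242/7 = 5.4 weeks (b = 0) or 40 - 227/7 = 7.6 weeks (b = 15). For L = 5 the share is 0.43/15 = 3% to 2.57/15 = 17%.

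**Other start date**

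5 June 2022 to 31 May 2023 is 360 days, or 51.4 weeks. A woman entering at 4 weeks needs 36 + 30/7 = 40.3 weeks, so that calendar holds everyone.

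**Length needed if the post-delivery end line stands**

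Entry at 4 weeks needs 40.3 weeks after the last baseline interview. An end at 42 weeks leaves 1.7 weeks for births after 40 weeks. With the 15-day baseline the total is 42 + 2.1 = 44.1 weeks, or 309 days: 67 days (about 2.2 months) more than 242.

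**The case against.** The strongest reply is that the shortfall depends on choices the protocol does not settle. With the June 2022 start it disappears. The work plan runs past May 2023, so 31 May 2023 may not be a hard stop. The intervention table puts the first two sessions in the second trimester; if most women enter then, almost nobody is cut off. All of this stands, so the shortfall has to be stated conditionally. It does not remove the contradiction: which calendar applies decides whether the end line fits.

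A second reply is that sections 4.11 and 4.17 describe repeated cross-sectional surveys, so the end line need not reach the women recruited. That is weak. The sessions go to recruited women, section 4.8 allows for loss to follow-up, and 4.17 also calls the data panel data.

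Three stronger readings are tempting, and the protocol does not support them.

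- A reader might infer that a third to a half of the women lose the delivery outcome. That share concerns the interview one month after birth. Place of birth and attendant can be recorded once the birth has happened, and the undelivered share is smaller.
- A reader might infer that only early entrants can receive every session before birth. A woman entering just under 20 weeks is at about 37.4 weeks after four months (17.4 weeks), so every eligible woman can complete the sessions before a 40-week birth.
- A reader might infer enrolment before ethics approval or registration, because recruitment is in the past tense ("Baseline recruitment and interviewing of women within study clusters began in June 5, 2022") and approval and registration in the future. The preceding sentence of the same section uses the future tense for randomisation, and the work plan lists ethical clearance before baseline. The tenses conflict in the text; they do not show early enrolment.

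**Conclusion.** The point holds as a contradiction in the protocol with a conditional consequence for follow-up. The start dates, the order of baseline and randomisation, and the length of baseline are irreconcilable as written.

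If section 4.1 is the true window, women entering below about 9.7 to 11.9 weeks cannot have the interview one month after a 40-week delivery. The size is uncertain because the protocol gives no gestational-age distribution: 31-46% under uniform entry over 5-20 weeks, roughly 15-55% under other lower limits and birth at 39 or 40 weeks, and near 0% if entry is mostly in the second trimester. The undelivered share at the close, 3-17% for uniform 5-20 weeks, straddles the 10% loss allowance. The calculation allows no time inside the window for pregnancy screening or training of religious leaders, which would make the fit worse.

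**What to change.** State one dated sequence, identical in sections 4.1 and 4.14, the Participant timeline and the work plan, and consistent with the duration in the Summary: approval and registration, randomisation, 15-day baseline, intervention, end line. Put approval and registration in a tense that matches their dates.

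Delete the clause in the Participant timeline that has baseline recruitment completed only after four months of intervention.

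Reconcile the four-month end line (4.11, 4.13, 4.14, opening of 4.17) with the end line one month after delivery (later in 4.17). If the latter stands, set the study end about 42 weeks or more after the last baseline interview, so that entry at 4 weeks and births after 40 weeks are covered.

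The cost is protocol wording plus about two to two and a half more months of end-line fieldwork than section 4.1 allows. If the June 2022 start is the true one, no extension is needed and only the dates have to be corrected.

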## 4.2 Study design

This study is a cluster randomized control trial to assess effectiveness of trained religious leaders’ engagement in maternal health education on maternal health behaviours. A total of five objectives will be answered from this study. Objectives 1, 2 and 3 are designed as a community-based cluster randomized control trial, which evaluates the effectiveness of trained religious leaders’ engagement in maternal health education on maternal health behaviours (ANC, SDS and knowledge of danger signs during pregnancy and child birth)**.** The fourth objective is designed as a cross-sectional study for the scale validation on engagement of religious leaders in promoting maternal health; the survey will assess how effectively the religious leaders deliver maternal education, to estimate dimensions of engagement. The fifth objective is qualitative study, designed as explorative grounded theory.

## 4.3 Source population

All pregnant women living in Misha district of Hadiya Zone, Southern Ethiopia.

## 4.4 Study population

Pregnant women in selected kebeles of district in Hadiya Zone, Southern Ethiopia

## 4.5 Inclusion and Exclusion Criteria

**Inclusion criteria**

- Pregnant women less than 20 weeks gestational age
- Living in selected kebele
- Pregnant women willing to participate in the study

**Exclusion Criteria**

- Pregnant women who are seriously ill and unable to communicate will be excluded from the study.

# 4.7 Study variables

## 4.7.1 Dependent variables

- ANC Utilization
- Skilled delivery service Utilization

## 4.7.1 Independent variables

**Socio-demographic and economic characteristics**

- Age
- Ethenicity
- Religion
- Income
- Marital status
- Educational status
- Occupation
- Family size
- Average distance from nearest HC

**Reproductive history of pregnant mothers**

- Parity
- Age at pregnancy
- Still birth
- Abortion
- Home delivery
- Institutional delivery
- Neonatal death

**Behavioural variables**

- Knowledge of the major obstetric danger signs
- Birth preparedness and complication readiness
- Attitude towards skilled delivery service utilization
- Perception of Pregnancy Risk
- Self-efficacy

All variables will be measured at the individual-level (i.e., for each pregnant mother) within study clusters.

## 4.8 Sample size

In accordance with the main objective of the larger study, the sample size estimate is designed to detect changes in the proportion of skilled delivery service utilization. The sample size is calculated using stata software based on the following assumptions. Tail (s): One; effect size (d): 0.15; **α** error probability = 0.05; power (1-**β** error probability) = 0.8, and allocation ratio (N1/N2) = 1. This gives a sample size of 155. Then, adding design effect, DE = 1+(m-1)ICC , where m=Average cluster size, m= 50, ICC=0.02 based on a published study ICC (Killip et al., 2004), DE=2, and allowing for a 10% loss to follow up, the total sample size is 682 (N1 = 341 and N2 = 341). N1 and N2 are sample sizes in the control and intervention group, respectively. Based on these assumptions, the estimated sample size is: 306 pregnant mothers per group to detect a 15-percentage point anticipated difference in the proportion of skilled delivery service utilization (an increase from 26% to 41%). This estimate is based on the baseline skilled delivery service utilization in the Ethiopia Demographic and Health Survey (26% from EDHS 2016, SNNP region report) in the control group (CSA, 2016).

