# Summary

Background: Despite the many supply- and demand-side interventions aimed at increasing uptake of maternal health service utilizations, the maternal and new-born health service utilizations remains low. Religious leaders have the power to inhibit or facilitate effective adoption of maternal health service utilizations to promote maternal and child health. However, evidence on the roles of religious leaders in promoting maternal health behaviour in developing world is not fully known. Therefore this cluster-randomized trial is designed to evaluate the effects of trained religious leaders’ engagement in maternal health service utilizations and knowledge of major obstetric danger signs.

Methods: A community based cluster randomized control trial in which the study kebeles are randomly assigned into intervention and control groups will be conducted. The sample size is calculated using stata software. Three hundred six pregnant mothers will be enrolled in each group. The intervention comprised of the messages on maternal health and new-born care by trained religious leaders. A baseline study will be conducted before the intervention and post-intervention evaluation will be conducted after four months. Religious leaders will be selected and trained to lead participatory sessions on maternal health and new-born care. Data on maternal health service utilizations, knowledge about obstetric danger signs, attitude towards skilled delivery service utilization and perception of pregnancy risk will be collected from a repeated cross sectional household survey. Effect of intervention will be assessed using multivariable logistic regression with generalized estimating equation model. Mixed-effects multilevel logistic regression model will be used to identify determinants of skilled delivery service utilizations. Data will be analyzed using STATA software. For qualitative study, coded transcripts will be further analyzed and summarized in narratives for each theme and sub-theme.

**Work plan and budget:** the project will take about one year for completion and the total estimated cost is 256,000 Birr.

**Key words:** Religious leaders, maternal health, Hadiya Zone

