## 1.1.5 Maternal Health Status in Ethiopia

Levels of utilization of ANC, delivery and PNC have been steadily increasing in Ethiopia as
shown by DHS data between 2000 and 2019. The national averages in 2000 were 27% for ANC, 5% for delivery care and 11% for PNC (CSA, 2001) but increased to 74%, 50% and 34% respectively by 2019 (EPHI, 2019). Similar upward trends have been observed in the SNNP region, with ANC having the highest consumption and PNC having the lowest. While ANC use, when measured as at least one visit, has generally been higher than other service use in Ethiopia, it is much lower when the proportion of women reporting four or more visits is considered. Nevertheless, the number of women reporting at least four ANC contacts has increased between 2000 (10%) and 2019 (43%) (EPHI, 2019, CSA, 2001). Pregnant women have also tended to begin using ANC in their second trimester rather than in their first trimester as recommended, and this has only marginally improved over time (CSA, 2016). The proportion of births attended by skilled professionals has been on the rise since 2000 (CSA, 2016, CSA, 2001). However, the majority of these births are assisted by nurses and midwives rather than doctors. In 2016 for example, only 20% of births were attended by doctors although the proportion is much higher in private facilities compared to government facilities (CSA, 2016). A shift in policy around clean and safe delivery at health posts may also have affected the profile of providers attending to births. Initially HEWs were trained to support uncomplicated deliveries at health posts (Medhanyie et al., 2012, Jackson and Hailemariam, 2016), but this policy was later discontinued possibly over concerns about the inability of all HEWs to perform this safely (Desta et al., 2017). The percentage of women receiving PNC from health professionals has also been slowly rising from just 3% in 2000 to 16% in 2016 (CSA, 2001, CSA, 2016). Most women receive their first postnatal check within the first 48 hours after delivery and numbers have been steadily increasing from just 2% in 2000 (49) to 34% in 2019 (EPHI, 2019). As with ANC, very few women have additional PNC visits beyond the first 48 hours as recommended. In fact in 2016, less than 2% of women reported postnatal checks between one and six weeks after birth (CSA, 2016).

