## Randomization

There are a total of 12 clusters for this cluster randomized trial. The researcher and kebele leaders, religious leaders and HEWs will conduct the randomization to produce comparable groups and eliminate the source of selection bias in the assignment of kebeles to the intervention and control groups. Simple randomization with a 1:1 allocation will be applied to assign clusters to either control or intervention groups. First, 12 nonadjacent clusters will be selected by a lottery method. Then, the 12 clusters were listed alphabetically. A list of random numbers will be generated in MS Excel 2010 and the generated values will be fixed by copying them as “values” next to the alphabetic list of the clusters. These are arranged in ascending order according to the generated random number. Finally, the first 6 clusters will be selected as intervention clusters and the last 6 as control clusters. A statistician that will be blinded to study groups and not participated in the trial will do the generation of the allocation sequence and the randomization of clusters (Figure below). The intervention group is assigned to receive training from religious leaders on maternal and neonatal health and the control group will be left to continue the current practices.

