## 4.11 Trial design

This study is a parallel two-arm a cluster randomized controlled trial with 8 clusters. The trial arms are as follows: 1) religious leader training and 2) standard cares. The kebeles health posts are designated as clusters for the trial. Outcome assessments will be made using repeat cross-sectional surveys at baseline (prior to intervention roll-out) and at 4 months post intervention (i.e. the end line). A schematic for the trial design is displayed in Figure 2.

Screening

Two districts out of 13 districts of Hadiya Zone selected purposely

Non-adjacent 12 kebeles from two districts selected randomly

Randomization

Cluster randomization of 12 clusters to 2 study groups

Intervention groups: (6 clusters)

Control groups: (6 clusters)

Recruitment

-Recruit pregnant mothers with gestational age less than 20 wks. (n =341)

- Baseline data collection

base line data collection

**-**Recruit pregnant with mothers with gestational age less than 20 wks. (n =341)

-Baseline data collection

Intervention

Training for pregnant mothers by trained religious leaders

The usual care only

End line

End line data collection

End line data collection

Figure 2: Diagrammatic representation of the randomization of study cluster (kebeles)

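### Section 4.8 states a one-tailed test but gives the two-sided n of 155, leaves 306 and 341 per arm unlabelled so that two enrolment targets result, and section 4.11 gives 8 clusters where the rest of the protocol gives 12

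*Protocol*

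**What the plan says.** Section 4.8 sizes the trial on skilled delivery, for a rise from 26% to 41%. It sets "Tail (s): One; effect size (d): 0.15", alpha 0.05, power 0.8 and equal allocation, and reports 155. It applies a design effect with average cluster size 50 and ICC 0.02, rounded to 2, and a 10% allowance for loss. On that basis "the total sample size is 682 (N1 = 341 and N2 = 341" per arm). Two sentences later it says: "Based on these assumptions, the estimated sample size is: 306 pregnant mothers per group to detect a 15-percentage point anticipated difference". Neither figure is labelled as enrolled or analysed.

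The Summary says: "Three hundred six pregnant mothers will be enrolled in each group". The flow diagram in section 4.11 recruits 341 in each arm.

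Section 4.11 opens with: "This study is a parallel two-arm a cluster randomized controlled trial with 8 clusters". The Randomization section says: "There are a total of 12 clusters for this cluster randomized trial". Sections 4.9, 4.12, 4.14 and 4.15, the list of kebeles in Table 1 and the flow diagram in 4.11 itself (6 + 6) also give 12.

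Section 4.19 plans GEE and random-effects logistic models. It does not say whether the test is one- or two-sided.

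**The concern.** Three basic design quantities are each given in two ways: the sidedness of the test, the number to enrol and the number of clusters.

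- **Sidedness.** Section 4.8 is the only place that states it. Taken literally, the trial could claim success at one-sided 5%, which is two-sided 10%, although its size was calculated for two-sided 5%.
- **Enrolment.** A field team working from the Summary would stop at 306 per arm, with nothing set aside for the loss that section 4.8 allows for.
- **Clusters.** With 8 clusters, the cluster size of 50 behind the design effect no longer holds.

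A further question is how firmly the 80% stands. The calculation uses normal quantiles and takes no account of how few clusters there are.

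**Working it through.** **Inputs (all section 4.8 except the cluster count):** p₁ = 0.26, p₂ = 0.41, difference 0.15, alpha 0.05, power 0.80, m = 50, ICC = 0.02, loss 10%. Clusters: 6 per arm (Randomization section).

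**1. The figure of 155.** Pooled two-proportion formula, with p̄ = 0.335:

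n = [z_α √(2p̄(1 − p̄)) + z_β √(p₁(1 − p₁) + p₂(1 − p₂))]² / (p₂ − p₁)²

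- Two-sided (z_α = 1.960, z_β = 0.842): 154.2, so **155**. The protocol's figure is reproduced exactly.
- One-tailed (z_α = 1.645): 121.4, so **122**.

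Other one-sided variants (unpooled, arcsine, continuity-corrected) run from 119 to 135. None gives 155.

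**2. The figures of 306 and 341.**

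- Design effect: 1 + 49 × 0.02 = 1.98, stated as 2.
- 155 × 1.98 = 306.9: the 306 (rounded down), before any allowance for loss.
- 155 × 2 × 1.1 = 341: the number with the allowance.
- Check: 341 × 0.9 = 306.9.

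So 341 is the number to enrol and about 306 the number expected to be analysed. Enrolling 306 leaves 306 × 0.9 = 275.

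A true one-tailed plan would run 122, then 122 × 1.98 = 242, then 242 / 0.9 = 269 per arm. The protocol gives none of these.

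**3. Power with 6 clusters per arm, ICC 0.02.** With n analysed per arm, cluster size is n/6 and DE = 1 + (n/6 − 1) × 0.02. Then SE = √[(0.1924 + 0.2419) × DE / n]. Normal power is Φ(0.15/SE − z). The t version uses a noncentral t on 12 − 2 = 10 df.

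| Enrolled per arm | Analysed | DE | 0.15/SE | Two-sided, normal | Two-sided, t (10 df) | One-sided, t (10 df) |
|---|---|---|---|---|---|---|
| 341 | 307 | 2.00 | 2.82 | 80.4% | 71.9% | 83.5% |
| 306 | 275 | 1.90 | 2.74 | 78% | 70% | 81.7% |

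With the pooled variance under the null, the two-sided normal figure for 306 analysed is 79.7%.

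**4. Dependence on the ICC** (two-sided, t on 10 df, 306 analysed): 83% at 0.01, 72% at 0.02, 62% at 0.03 and 49% at 0.05.

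**The case against.** Four points can be made in the protocol's favour.

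- **The errors are mild in effect.** Having 155 where a one-tailed test needs 122 errs on the safe side. Stopping at 306 instead of 341 costs about 2 points of power. The 8 is an isolated slip, contradicted by the flow diagram in the same section. All of this stands. It limits the damage but leaves the figures wrong as written.
- **A reader might infer that 12 clusters do not deliver the stated 80% power.** The protocol does not support that as a flat statement. By its own two-sided normal method, 341 enrolled gives 80.4%. Under its stated one-tailed test, power is 83.5% even on 10 df. The fall to about 72% needs a two-sided test and a t reference together, and the protocol specifies neither. A small-sample correction for GEE may properly sit in an analysis plan that is not shown.
- **A reader might also call the 26% control rate out of date**, because section 1.1.5 reports that use of antenatal, delivery and postnatal care "increased to 74%, 50% and 34% respectively by 2019". That 50% for delivery care is a national average. The 26% is the regional figure, the trial is in two rural districts, and section 1.1.6 gives 21% skilled attendance for rural births in 2016. The protocol gives no newer local rate, so restating power at 50% is not warranted.
- **A reader might doubt that 682 eligible women can be found**, working from the expected pregnancies in section 4.1. Depending on whether those are read as annual or point-in-time counts, plausible yields fall on both sides of 682. No shortfall is shown.

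**Conclusion.** The three contradictions hold and need no outside assumption.

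- The stated one-tailed input does not give 155; a two-sided 5% test does.
- 306 and 341 are the analysed and enrolled numbers for the same calculation. The Summary uses the analysed number as the enrolment target, which would leave about 275 per arm and 78% power by the two-sided normal method.
- The 8 clusters in 4.11 conflict with 12 everywhere else. Power under 8 clusters describes a design that the rest of the protocol does not plan, so it should not be read as the trial's power.

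On power, the conclusion is conditional: if the test is two-sided, as 155 implies, and allows for only 12 clusters (t on 10 df, ICC 0.02, about 306 analysed per arm), power is about 72%. The 80% is right only under the normal design-effect approximation.

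**What to change.** - **Section 4.8:** state a two-sided 5% test; 155 per arm before clustering; 341 per arm enrolled and about 306 analysed after 10% loss; 12 clusters, 6 per arm.
- **Summary:** change the number enrolled per group from 306 to 341.
- **Section 4.11:** change 8 clusters to 12.
- **Section 4.8, one added sentence:** the 80% rests on the normal design-effect approximation; with a two-sided test referred to a t distribution on 10 df at ICC 0.02, power is about 72%.

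The cost is protocol wording and a less favourable stated power. No women are needed beyond the 341 per arm already planned, and neither the control rate nor the recruitment schedule has to change on this account.
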